#### Completed the study

Patients will be considered as having ‘completed the study’ if they have attended at least the first and last scheduled visit at 6 months.

#### Baseline drop-out population

All patients enrolled who dropped out before the start of randomized treatment.

### **9.3 Descriptive Analyses**

All available data will be analysed descriptively for each intervention group. Results will be summarised as frequencies and percentages for nominal data; as means, standard deviations, range, and 95%-confidence intervals for continuous data; and as medians, quartiles, and ranges for ordinal data.

Differences regarding baseline variables will be analysed by appropriate tests (e.g. Chi squared test, Kruskal-Wallis test, or analyses of variance) in pair wise comparisons between the three treatment groups, and will additionally be checked for clinical relevance.

#### **9.3.1 Primary analysis of the primary endpoint**

The primary endpoint is “negative nutritional outcome” of a child within the 6 months follow-up period as defined in section 8.8.1. The incidence rate (in formulae below referred to simply as ‘rate’) of “negative nutritional outcome” will be computed as the number of events divided by total observed person-time in each treatment group. As an “event” the first time a child reaches a negative nutritional outcome will be used. The primary analysis of the primary endpoint will be performed on the intention to treat population with no imputation of missing data.

In the primary analysis, RUTF will be compared to the control group.  
The hypotheses in this step are

$$\begin{aligned} H_0: \text{rate}_{\text{RUTF}} &= \text{rate}_{\text{Control}} \\ \text{vs.} \\ H_1: \text{rate}_{\text{RUTF}} &\neq \text{rate}_{\text{Control}} \end{aligned}$$

where  $\text{rate}_{\text{RUTF}}$  = rate of “negative nutritional outcome” in the children in the RUTF group, and  $\text{rate}_{\text{Control}}$  = rate of “negative nutritional outcome” in the children in the control group.

The comparison of rates among the treatment groups will be performed by a Poisson regression model, adjusted for nutritional status at enrolment (fixed effect) and will be performed within one model including the three intervention groups with contrasts for each two-group comparison. Tests will be two-sided with a significance level of 0.05.

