### **3. STUDY DESIGN**

This is a randomized controlled trial with three study groups. Children 6 to 59 months of age presenting at the OPD in Kaabong Hospital Kaabong district, Karamoja region and diagnosed with one or more of the three study diseases (malaria, diarrhoea and LRTI) are eligible for the study.

Children participating in this study will be randomised to one of the three groups to:

- A) Receive 14 days of RUTF supplementation with standard care and treatment or
- B) 14 days MNP supplementation with standard care and treatment
- C) Be included in a control group receiving standard care and treatment but not receiving nutritional supplementation (control group)

Individual follow-up will be 6 months. During this time, children in the RUTF or MNP group will receive 14 days nutritional supplement every time diagnosed with at least one of the three study diseases, not exceeding more than 14 days supplementation in any 28 day period.

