## **8.7 Withdrawal procedures**

Children will be withdrawn from the study if:

- i.) Participant fulfils criteria for acute malnutrition during follow-up period.
- ii.) There is a serious protocol violation
- iii.) Participant is erroneously included
- iv.) There is the risk that the nutritional supplement would negatively influence a prescribed medical protocol (i.e. medical treatment has priority).

Patients who become acute malnourished will be referred to MoH/Action Against Hunger (AAH) Supplementary and Therapeutic Feeding Program for care and treatment.

Participants who are withdrawn from the study will continue to be followed up if possible and monitored following standard study protocol. The use of data for analysis from withdrawn participants will be assessed by the study statistician.

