## **8.8 Endpoints**

### **8.8.1 Primary endpoint**

The primary endpoint is “negative nutritional outcome (NNO)” of a child within the 6 months follow-up period. The incidence of a negative nutritional outcome will be defined according to the baseline nutritional status.

- i) for children with no malnourishment at time of entry into study, “negative nutritional outcome” is defined as progression to moderate or severe malnourishment

Thus, the event of a child reaching a “negative nutritional outcome” at least once within 6 months of follow-up period will be compared between the three study groups.

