## **9. DATA ANALYSIS**

## **9.1 Sample size\***

The sample size is based on the primary hypothesis: Supplementation for 14 days with RUTF, concurrent to appropriate medical treatment for malaria, and/or LRTI, and/or diarrhoea reduces the incidence of malnutrition.

The sample size calculation is based on a combined incidence of moderate and severe malnutrition amongst children who are sick.

There are hardly studies reporting the incidence of malnutrition and no studies reporting incidence of malnutrition among sick children. Therefore for the purpose of these calculations, we assume that the incidence is estimated by dividing the prevalence of malnutrition by the period of having malnutrition times 6 months:  $= [(Prevalence / Duration\ of\ moderate\ malnutrition) * 6\ months]$

The estimated incidence for moderate and for severe malnutrition will be added to result in the incidence of negative outcome as defined as primary endpoint of this study.

The prevalence of moderate malnutrition among sick children is 15.5% and the prevalence of severely malnutrition among sick children is 7.2% according to the results if we take the survey done by MSF-OCA at February 2009.

Literature gives a duration of malnutrition (untreated) is estimated to be 7.5 months [29] and the duration of severe malnutrition is estimated at 4 months at the time of the survey. As duration of malnutrition might be different in the context of Karamoja we varied assumptions in order to use the lowest incidence as a basis for the sample size. This results in sample size that is large enough to give enough statistical power for the primary hypothesis (the sample size increases with a decreasing incidence). Increasing the prevalence of malnutrition in general or decreasing the duration of severe malnutrition (as there is treatment available) resulted in a higher incidence, but prolonging the duration of moderate malnutrition to 10 months gives a lower incidence.

Therefore the incidence is based on duration of 4 months for severe malnutrition and duration of 10 months for moderate malnutrition.

This results in an incidence of 0.201 per 6 months

Formula:  $0.201 = [(0.155 / 10 + 0.072 / 4)] * 6$

The assumed incidence rate in the control group (baseline incidence) is 0.20. A 30% reduction in the supplementation group, which is considered a clinically and operationally relevant improvement, results in an assumed incidence rate of 0.14 in each of the two interventions groups.

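### As worded, the denominator of the primary rate can include time after a child's first event, so the rate ratio depends on how fully withdrawn children are followed

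*Protocol*

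**What the plan says.** Section 9.3.1 defines the primary quantity as an incidence rate of NNO that "will be computed as the number of events divided by total observed person-time in each treatment group". For the numerator, "the first time a child reaches a negative nutritional outcome will be used". Rates are compared by Poisson regression, and the hypotheses are written on rates.

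Section 8.7 lists as a reason for withdrawal: "Participant fulfils criteria for acute malnutrition during follow-up period". The endpoint is progression to moderate or severe malnutrition, so a child who reaches it also meets a withdrawal criterion. The same section continues: "Participants who are withdrawn from the study will continue to be followed up if possible and monitored following standard study protocol". It then adds: "The use of data for analysis from withdrawn participants will be assessed by the study statistician".

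Section 8.8.1 describes the endpoint differently, as a child reaching an NNO "at least once within 6 months of follow-up period will be compared between the three study groups". That reads as a 6-month risk rather than a rate.

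**The concern.** If only first events count, a child leaves the risk set at that event. Time observed afterwards cannot produce another counted event, so it does not belong in the denominator of a first-event rate. The wording of 9.3.1 takes all observed time, 8.7 foresees observation after the event, and no section stops the clock.

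Taken literally, the primary rate ratio then depends partly on how many withdrawn children continue to be seen. If that share is the same in each arm, the arm with more events gains more of this extra time and the ratio is diluted. If the share differs, the ratio shifts for reasons unrelated to the incidence of malnutrition. Section 6.2 states that participants are not blinded to their group, so equal attendance after withdrawal cannot simply be assumed.

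**Working it through.** **Inputs from the protocol.** Section 9.1: "The assumed incidence rate in the control group (baseline incidence) is 0.20", per 6 months, with 0.14 under intervention, 660 children per group, 80% power and 5% significance. Section 9.3.1: two-sided test. Section 3: "Individual follow-up will be 6 months"; Table 1 puts the final visit at day 168.

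**Assumptions not in the protocol.** The hazard is constant. The share f of post-event time that is actually observed is unknown, so it is varied from 0 to 1.

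**The plan's own figure.** The usual Poisson-regression formula with allocation 0.5 is

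N = [1.960·√4 + 0.842·√(2 + 2/0.7)]² / (0.20·(ln 0.7)²) = 1311.

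The protocol states 1320, at which this formula gives power of 80.3%. For drop-out, 660/0.9 rounds up to 734, and 3 × 734 = 2202. The stated sample size reproduces and does not depend on this point.

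**Effect of the denominator.** Measure time in units of 6 months, with hazard h:

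- 6-month risk: r = 1 − exp(−h), which is 0.1813 (control) and 0.1306 (RUTF).
- Mean time at risk per child: a = r/h, which is 0.9063 and 0.9332.
- Denominator per child: D = a + f(1 − a).
- Rate: r/D.

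| Share of post-event time observed, control / RUTF | Control rate | RUTF rate | Ratio |
|---|---|---|---|
| 0 / 0 (time ends at NNO) | 0.200 | 0.140 | 0.700 |
| 50% / 50% | 0.190 | 0.135 | 0.711 |
| 100% / 100% | 0.181 | 0.131 | 0.721 |
| 80% / 40% | 0.185 | 0.136 | 0.737 |
| 40% / 80% | 0.192 | 0.132 | 0.689 |
| 100% / 0 | 0.181 | 0.140 | 0.772 |
| 0 / 100% | 0.200 | 0.131 | 0.653 |

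As an example, for 80%/40% the denominators are 0.9063 + 0.8 × 0.0937 = 0.9813 and 0.9332 + 0.4 × 0.0668 = 0.9599. The ratio is (0.1306/0.9599)/(0.1813/0.9813) = 0.737.

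**No true effect** (hazard 0.20 in both arms). Equal follow-up gives exactly 1.00. The extremes 100%/0 and 0/100% give 1/0.9063 = 1.10 and 0.9063/1 = 0.91.

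**Power and standard error at 660 per group.** The Poisson standard error of the log ratio is √[(1/0.1813 + 1/0.1306)/660] = 0.141.

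- Time ended at NNO: Φ(0.357/0.141 − 1.96), about 71%.
- All post-event time counted: Φ(0.328/0.141 − 1.96), about 64%.
- In the second case the estimator is a ratio of two proportions. Its true standard error is √[(1/0.1813 + 1/0.1306 − 2)/660] = 0.130, so the Poisson value is about 9% too wide. Allowing for this, power is Φ((0.328 − 1.96 × 0.141)/0.130), about 65%.

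The loss is therefore 6 to 7 points. The 71% starting value already lies below 80% because a different approximation is used and because first events number 660 × 0.181 in control rather than 660 × 0.20. Neither comes from the denominator.

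**Sensitivity.**

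- If events are detected only at scheduled visits, the ratio runs from 0.704 (time ended at detection) to 0.719 (all time counted).
- If 0.20 and 0.14 are read as 6-month risks, it runs from 0.676 to 0.700.
- With a control hazard of 0.4 or 0.6 and all time counted, it is 0.741 or 0.760.

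**The case against.** The best reply is that this is an ambiguity rather than an error. An incidence rate of first events is ordinarily computed on time at risk. Section 8.7 calls these children withdrawn and leaves use of their data to the statistician. Section 9.3.5 promises a detailed analysis plan, which could settle where time stops. Continued follow-up also has a purpose outside the primary rate, since 8.8.2 lists the number of NNOs, mortality, morbidity and end-of-study weight. This stands in part: the protocol does not expressly put post-event time into the denominator, and a reader who infers that it will certainly be counted goes too far. But the protocol is not silent. It states a denominator for its primary rate, and an analysis plan that stopped time at the event would depart from those words. Leaving the matter to later assessment affects every child with the primary event.

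A second reply is that, with complete follow-up, the result is simply the 6-month risk ratio, which matches 8.8.1. That is correct, and it is a legitimate quantity. However, 8.7 promises follow-up only where possible. With partial follow-up the result is neither an at-risk rate nor a risk.

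A third reply is that unequal follow-up is speculative. Section 8.9 has outreach workers trace missed visits, and section 11.1 gives compensation at scheduled visits without reference to arm. This stands: the protocol gives no figure for retention after withdrawal, and the unequal splits above are illustrations only.

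**Conclusion.** The denominator in 9.3.1 should be corrected. On its literal wording, the primary rate ratio varies with how much post-withdrawal follow-up is achieved. Under a constant hazard at the planned rates the effect is modest: 0.70 becomes at most 0.72 with equal and complete follow-up, with 6 to 7 points less power and a slightly conservative standard error.

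Three stronger readings are not supported:

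- **The ratio is always pulled towards 1.** This holds when post-event follow-up is similar in the arms or higher in control. If control children return less often, which a reader might expect because they receive no supplement, the ratio moves away from 1: 50% in control and 90% in RUTF gives 0.692.
- **The primary test is invalid.** With equal follow-up and no true effect the ratio is exactly 1. A spurious difference needs unequal follow-up, and even the extremes give only 1.10 and 0.91.
- **The sample size is wrong because of this.** The stated figure reproduces without reference to post-event time.

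**What to change.** In section 9.3.1, replace the stated denominator with: *person-time at risk, from randomisation to the earliest of first NNO, death, last nutritional assessment or day 168*. State that the log of this time is the offset in the Poisson model. Add that data after the first NNO are used only for secondary endpoints, so the statistician's assessment under 8.7 no longer bears on the primary rate. Any analysis plan should carry the same definition.

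The cost is a sentence or two. It needs no new data, changes no visit or clinical procedure, and leaves the sample size as it is.

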## **Glossary**

|                                   |                                                                     |
|-----------------------------------|---------------------------------------------------------------------|
| Not malnourished                  | W/H $\geq$ -2 z-scores                                              |
| Moderate acute malnutrition (MAM) | W/H $<$ -2 and $\geq$ -3 z-scores
MUAC $\geq$ 115mm to $<$ 125mm |
| Severe acute malnutrition (SAM)   | W/H $<$ -3 z-scores or
MUAC $<$ 115 or
Bilateral oedema       |
| Acute malnutrition:               | Includes either SAM or MAM                                          |
| Global acute malnutrition (GAM)   | W/H $<$ -2 z-scores or
MUAC $<$ 125 or
Bilateral oedema       |
| Rate of weight change             | Grams weight change / kg body weight at inclusion / days follow-up  |

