***Inclusion criteria***

6 to 59 months of age.

Non-acutely malnourished children.

Diagnosis of malaria and/or diarrhoea and/or LRTI.

Intention to remain in area for the duration of the 6 month follow-up.

Lives within approximately 60 minutes walking distance from the clinic.

Informed consent from a guardian.

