#### **4.2 Inclusion criteria**

Children will be included if they meet all the following inclusion criteria:

- 6 to 59 months of age
- Not malnourished children
- Diagnosis of malaria and/or diarrhoea and/or LRTI
- Intending to remain in area for the duration of the 6 month follow-up
- Living within approximately 60 minutes walking distance from the clinic
- Informed consent from a guardian\*

\* Parent or other legal guardian. If not a parent, must be at least 18 years of age

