#### **4.3 Exclusion criteria**

Children will not be included if they meet any one of the following exclusion criteria:

- Child is exclusively breastfeeding
- Child is acute malnourished
- Presence of 'General Danger Signs'
- Presence of severe disease (including severe malaria, severe LRTI, severe diarrhoea)
- Needing hospitalisation for any reason
- Known history of allergy to the nutritional supplementation
- Having a sibling enrolled in the study\*

---

\*Until March 2010 MSF was supporting the MoH structure with on the job training for MoH staff.

† \*Information on the determination of the sample size is elaborated in section 9.1

\*When one twin child is recruited, the twin sibling cannot be recruited but will receive the same supplement. This is done to limit the risk that, given the unique nature of twins, a guardian may share supplementation with twin siblings.

Patients who do not meet all eligibility requirements and/or who fulfil any one exclusion criteria at screening will be considered not eligible for participation (See Annex f1-screening form).

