In addition, in case of significant and/or relevant differences of baseline values additional adjustment(s) for these factors will be performed within the model described above (in models with and without interaction), to address the potentially confounding or effect modifying effect of other variables. These variables include age (in months and binary: <36 months,  $\geq 36$  months), gender, breastfeeding practices, cough, underlying illnesses, socio-economic factors, food availability, length of illness before visiting MSF clinic, other health support sought during study, season during which child was in the study.

The amount and pattern of missing data of the primary endpoint will be checked by a person blinded to treatment allocation, and a decision based upon the result of this check will be made as to whether and how the imputation of missing primary endpoint data will be performed.

Additionally, the 6-months follow-up period will be split and analysed separately for 1 month periods with the method described above.

The analysis of the primary endpoints will also be repeated as described above separately for children with no malnourishment at time of entry into study and children with moderate malnourishment at time of entry into study.

The analysis of the primary endpoint will be repeated as described above for the per protocol population.

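### The only covariate in the primary model has a single level among eligible children, and the secondary adjustment list contains a post-randomisation variable

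*Protocol*

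**What the plan says.** Protocol section 9.3.1 compares the arms in one Poisson model, "adjusted for nutritional status at enrolment (fixed effect". No other covariate is named for the primary analysis.

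Eligibility restricts that same characteristic. Section 4.2 requires "Not malnourished children" (the Executive Summary has "Non-acutely malnourished children"), and section 4.3 excludes on "Child is acute malnourished". The Glossary entry for acute malnutrition reads "Includes either SAM or MAM", so moderate cases are kept out as well as severe ones.

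Section 8.8.1 announces an endpoint definition that depends on baseline nutritional status, but lists only the category without malnourishment. Section 9.3.2 nevertheless repeats the analysis for a second category, "children with moderate malnourishment at time of entry into study".

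Section 9.3.2 also provides that "in case of significant and/or relevant differences of baseline values additional adjustment(s) for these factors will be performed within the model described above". Its list of candidate variables includes "other health support sought during study".

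**The concern.** A factor that takes the same value for every child cannot adjust for anything. As written, the protocol promises an adjusted primary analysis and delivers an unadjusted one, although weight and height are measured on every child at day 0 (section 8.1, Table 1). The endpoint is largely a matter of crossing a weight-for-height threshold, so distance from that threshold at entry is a plausible predictor. Some precision may be given up for no reason.

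The second issue is different in kind. The adjustment rule in 9.3.2 is triggered by differences in baseline values, but outside care sought during follow-up is not a baseline value. Section 6.2 states that participants are not blinded, so allocation could influence where families seek care. Conditioning on a variable that treatment can affect may bias the estimated treatment effect, even in a randomised trial.

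**Working it through.** **1. The plan's own sample size.** Inputs from section 9.1: control rate 0.20, rate ratio 0.7, two-sided 0.05, 80% power, equal allocation (p = 0.5). The usual formula for Poisson regression with a binary covariate is

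N = [z(0.975)·√(1/(p(1−p))) + z(0.80)·√(1/(1−p) + 1/(p·RR))]² / (rate₀·(ln RR)²)

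= [1.960 × 2 + 0.8416 × √(2 + 2/0.7)]² / (0.20 × 0.1272) = 1311.

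The protocol states 1320, at which the formula gives 80.3% power. Drop-out: 660/0.9 rounds up to 734, and 3 × 734 = 2202, as stated. The figure is reproduced without any allowance for a covariate, so nothing below changes it.

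**2. Levels of the covariate.** Set the sections side by side:

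| Status at entry | Eligible (4.2, 4.3, Glossary)? | Used in analysis (8.8.1, 9.3.2)? |
|---|---|---|
| None | Yes | Yes |
| Moderate | No | Yes, in 9.3.2 |
| Severe | No | No |

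Only the first row can contain eligible children. Children enrolled in error are the one possible exception, and section 8.7 has them withdrawn.

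**3. Effect on the model.** Take an intercept, two arm indicators and a status indicator with every child at the same level. The design matrix has 4 columns and rank 3. In one simulated trial with 734 per arm, the log rate ratios against control were −0.283 (SE 0.125) and −0.457 (SE 0.131), identical with and without the status term. The adjusted model is the unadjusted model.

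**4. What a varying covariate would add.** These are simulations with 660 per group, 1,500 trials per setting, and a weight-for-height z-score distributed N(−0.6, 1) truncated at −2. The z-score distribution and the hazard gradients are assumptions; the protocol gives neither. With six-month risks set to 0.20 and 0.14:

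| Hazard increase per z-score lower | Unadjusted power | Adjusted power | Gain (points) |
|---|---|---|---|
| 2-fold | 84% | 86% | 2 |
| 3-fold | 84% | 88% | 4 |
| 5-fold | 82% | 91% | 9 |

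The alternative calibration fixes the ratio within z-score at 0.7 and overall risk at 18% (1 − e^(−0.20) = 0.18). Over repeated runs under both calibrations the gains were about 2 to 3, 4 to 7 and 8 to 14 points. When the z-score had no prognostic effect, power was the same with and without it. The simulation error of a single power near 80% is √(0.8 × 0.2/1500), about 1 point.

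**5. The adjustment list.** Age, sex, breastfeeding and length of illness before the visit are fixed at entry. Season is largely fixed by enrolment date. Other health support during the study is not: it accrues over the six months in which the endpoint is also accruing.

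**The case against.** Section 9.3.1 gives no coding for the covariate. Section 8.3 says nutritional status is assessed by weight-for-height, MUAC and oedema, and the first two vary among eligible children. The label of fixed effect does not by itself mean a category, and section 9.3.5 leaves detail to a SAP. This has force: a continuous covariate may have been intended. But the protocol names none, and sections 8.8.1 and 9.3.2 both treat status as categories. Section 9.3.2 also commits to an analysis with no eligible children, which coding in a SAP cannot repair.

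Three stronger readings are tempting, and the documents do not support them.

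- A reader might infer that the primary test is invalid or underpowered because of the empty factor. An unadjusted randomised comparison is valid. Simulated unadjusted powers of 64 to 70% arise only when the ratio within z-score is fixed at 0.7 and overall risk at 18%. At the protocol's own 0.20 against 0.14, unadjusted power is about 82 to 84%.
- A reader might infer that further covariates are picked by significance tests alone. The trigger is significance and/or relevance, and section 9.3 adds a check for clinical relevance.
- A reader might take section 8.2 as the protocol's own admission that allocation changes outside care. That passage concerns unscheduled visits made to obtain more supplement, and is given as a reason for the 28-day limit. It does not address other health support. The case against that variable rests on its timing and the lack of blinding.

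It also stands that any bias is confined to a conditional secondary model in 9.3.2.

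**Conclusion.** The point holds in limited form. In the categories the protocol uses, the sole primary covariate is constant, the primary analysis is valid but effectively unadjusted, and the moderate-malnourishment analysis is empty. The cost is forgone precision: roughly 2 to 14 points of power, depending on calibration and on an assumed 2- to 5-fold hazard gradient per z-score, and nothing if the z-score is not prognostic. Separately, one listed adjustment variable is measured after randomisation and could bias the secondary adjusted estimate. The documents give no basis for the size or direction of that bias. Both should be corrected before analysis. Neither threatens the primary test or the sample size.

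**What to change.** - **Section 9.3.1:** name the continuous weight-for-height z-score at day 0 as the covariate, in place of nutritional status at enrolment.
- **Section 9.3.2:** delete the separate analysis of moderately malnourished entrants. Limit the adjusted sensitivity model to a list of day-0 variables fixed in advance, in place of a choice triggered by observed baseline differences. Remove "other health support sought during study" from the list; it can still be described by arm.

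The cost is wording only. Weight and height are already taken at day 0, and no sample-size figure moves. The one change in meaning is that the treatment estimate becomes conditional on the baseline z-score, which the report should state; an unadjusted estimate can be shown beside it.
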